### 2.2. Setting

Anthropometric data will be collected from the participants who fulfill the selection criteria between the first and second semesters of the 2023 academic year. This research will be conducted with the support of the Universidad CES as part of the thesis activities required by the Master of Science in Sports Nutrition degree program. Experimental procedures for developing and cross-validating the new equations will be conducted, as in previous studies carried out by our research group [42,43].

### 2.3. Participants

The study population will be healthy, male and female residents of Medellín and the nearby municipalities that make up its metropolitan area (the Andean Region of Colombia), who exhibit different levels of physical activity. The sample of the sedentary population will be obtained through an open call to both students and administrative personnel at Universidad CES. The sample of the physically active population will be obtained from the collaboration agreement between DBSS International and Smart Fit Colombia, for which a sample of personalized trainers working in Medellín and its metropolitan area will be used. Finally, the sample of professional athletes will be obtained by taking advantage of the interinstitutional relations of the Research Division of DBSS International and the IPS ARTHROS—Physiotherapy and Exercise Center with clubs and sports entities in Antioquia.

In order to comply with the objectives of this research, the following will be taken into consideration as inclusion criteria: (i) +18 years old (under 60 years); (ii) residing in the city of Medellín or nearby municipalities of the metropolitan area; (iii) low, moderate, and high categories, according to the IPAQ-SF questionnaire [44] for sedentary, physically active, and athletes, respectively. In addition, athletes will need to demonstrate previous experience in sports events (>1 year) and current affiliation with a club team participating in league games or sanctioned tournaments; (iv) signed, informed consent to submit to the anthropometric and DXA measurements. The following participants will be excluded: (i) those individuals diagnosed with a disease and/or a special condition that limits exposure to radiation emitted by DXA; (ii) adults over 60 years of age; (iii) pregnant women; (iv) athletes with injuries; and (v) people with implants or prostheses. All procedures will be developed in accordance with the latest version of the Declaration of Helsinki [45]. The study protocol has been approved by the Research and Innovation Committee at the University CES (Acta0031Proy115TG) and registered with ClinicalTrials.gov (ID #NCT05450588).

### 2.4. Variables

As reference criteria, whole and regional body composition will be estimated using DXA. The restricted-profile anthropometric variables established by ISAK will be measured: basic measurements; skinfolds (mm); girths (cm); lengths and heights (cm); and breadths and depths (cm). We will also estimate body composition based on anthropometric data.

### 2.5. Data Sources/Measurement

All of the measurements for the selected participants will be performed at the research center CESNUTRAL at CES University and the facilities of the IPS ARTHROS—Physiotherapy and Exercise Center (Medellín, Colombia). To reduce technical errors in measurement, the evaluations will be conducted between 9:00 and 17:00 (GMT-5) at controlled environmental conditions (<24 °C and <60% humidity).

#### 2.5.1. Body Composition

DXA measurements will be performed following all current recommendations and the laboratory procedures reported in previous articles published by our research group [46,47,48]. To perform the scans, a Lunar Prodigy™ unit will be used (General Electric Healthcare, Madison, WI, USA). Each subject will be scanned by a certified bone densitometry technologist, and the distinguished bone and soft tissue, edge detection, and regional demarcations will be performed using computer algorithms.

#### 2.5.2. Anthropometry

All anthropometric measurements will be carried out in accordance with the International Standards for Anthropometric Assessment published by the ISAK [12]. Body mass will be measured with a digital scale to the nearest 100 g (Seca 874, Hamburg, Germany). A portable stadiometer with a 1 mm graduation will be used to measure stature and wingspan (Seca 213, Hamburg, Germany). A 50 cm high wooden anthropometric box will be used to measure the sitting height. The skinfold thicknesses will be measured with a calibrated skinfold caliper (Harpenden, UK). Girths will be measured with a non-extensible metal tape with a thickness of 0.7 cm (Lufkin w606PM, Apex Tool Group, Sparks, MD, USA). The measurement of breadths will be performed with a Realmet Petit (16 cm) small sliding caliper (Realmet, Barcelona, Spain). Averages based on two measurements of anthropometric data will be calculated and analyzed.

#### 2.5.3. Anthropometry-Based Analysis of Body Composition

We will estimate whole-body-fat percentage (as RFM) in sedentary and physically active individuals following procedures conducted by Woolcott and Bergman [26]. The Takai et al., equation [35] will be used to estimate fat-free mass in athletes. We will also report the sum of skinfolds (∑S) as an absolute variable (expressed in millimeters) which not only gives information about the local distribution of subcutaneous fat tissue, but which also indicates whole-body adiposity since it correlates with whole-body-fat mass [40,49]. As a musculoskeletal index, the skinfold-corrected muscle girths for arm, chest, waist, thigh, and calf will be calculated according to the expression: girth—(π × skinfold) [50].

### 2.6. Bias

The different types of intentional or unintentional bias and error that may occur in this study will be controlled according to their nature: (i) Gross errors—daily calibrated, certified, and recognized by international entities or Colombian technical regulations and legal metrology (Superintendence of Industry and Commerce) equipment and instruments will be used; (ii) Pre-analytical errors (blunders)—the research assistance personnel will be previously trained in the annotation and accompaniment at the moment of recording the data using a specific typography and computer files for databases. The recorder assistant will always repeat the value dictated by the anthropometrist at the time of the assessment; (iii) Systematic errors—the relative technical error of measurement of the technicians will be reported. We will ensure that the intra-observer technical error of measurement of the certified anthropometrists (√[∑differences^2^/2n]) will be less than 7.5% for skinfolds and less than 1.5% for the other measurements, which is considered acceptable by the ISAK recommendations [10]. The coefficient of variation of the DXA equipment will be reported (CV% = Standard Deviation/Average × 100%). The test–retest reliability of the DXA unit that will be used in this study has shown a coefficient of variation ranging from 1.0 to 2.0%. In addition, similar to previous reports [46], we will adjust the DXA measurements based on the model proposed by Heymsfield et al. [51] to eliminate the influence of fat-free adipose tissue (FFAT) on DXA-derived fat-free mass. This has been shown to provide more accurate values to detect changes in body composition [52]. Therefore, we will estimate the adipose tissue as DXA-fat mass ÷ 0.85; FFAT will be then calculated as adipose tissue × 0.15; and, finally, DXA-derived fat-free mass will be adjusted with the subtraction of FFAT.

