Several authors have concluded that regression equations that use WG as a predictive variable appear to estimate body fat percentage more accurately [23,24,25]. In this sense, the relatively recent efforts of some research groups have developed equations that include WG as an independent variable to estimate fat mass and fat-free mass. On the one hand, Woolcott and Bergman [26] developed and validated a simple equation, named relative fat mass (RFM), to estimate the percentage of total body fat using the WG, stature, and sex of the American adult population (64 − (20 × (stature [m]/WG [m])) +  (12 × sex [0 for male and 1 for female])). The population data were extracted from the National Health and Nutrition Examination Survey (NHANES) between 1999 and 2006. The performance of RFM as an easy and useful tool in clinical practice, with a better correlation to DXA than BMI (RFM: R^2^ = 0.84; RMSE = 3.51% vs. BMI: R^2^ = 0.36; RMSE = 7.04%) has been validated in adults [27], children between 8 and 14 years old, and adolescents between 15 and 19 years old [28], obese subjects [29,30], and individuals with Down syndrome [31], among other populations at cardiovascular risk [32,33]. It is worth noting that the RFM defines obesity according to the cutoff points of the DXA measurements, to the point that following the rounded thresholds of the RFM baseline, the current recommendation for diagnosing obesity and predicting the risk of death with this parameter is 40% for women and 30% for men [34]. On the other hand, Takai et al. [35] developed an equation to estimate fat-free mass in male athletes using some indices as independent variables, including WG/body mass and stature/WG. The equation developed by these authors was validated with a sample of 48 athletes from different disciplines and showed a high correlation (R^2^ = 0.900, SEE = 2.3 kg [3.8%]) with the fat-free-mass data obtained by DXA (FFM (kg) = 0.883 × Body mass/WG [kg/m] + 43.674 × WG/Stature [cm/cm] − 41.480). The results of this study demonstrated that an equation using body mass and stature ratios with WG as independent variables is applicable and useful for predicting fat-free mass in male athletes.

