### 2.8. Statistical Methods

The descriptive analysis of the anthropometric characteristics of the study population will be reported as means, standard deviations, and 95% confidence intervals. First, the total sample of participants will be used for the external validation of the RFM (to estimate whole-body-fat percentage) [26] and the Takai et al., equation (to estimate fat-free mass) [35]. A correlation analysis will be performed by calculating Pearson’s r, intraclass correlation coefficient (ICC), concordance correlation coefficient (ρ_c_), adjusted coefficient of determination (aR^2^), and root mean squared error (RMSE) as compared to DXA measurements. Smaller values of standard error of the estimate (SEE) and RMSE will indicate that the estimated values are closer to the DXA measurements. Bland–Altman diagrams will be used for the concordance analysis. This is a procedure to determine whether two measurement methods, X and Y, agree sufficiently to be declared interchangeable (D = X − Y). The mean of these differences represents the systematic error (bias), while the variance of these differences (1.96 SD) measures the dispersion of the random error.

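### Subtracting fat-free adipose tissue from the DXA reference adds about 0.18 kg per kg of fat to the measured bias of the published fat-free-mass equation, if that equation predicts unadjusted DXA fat-free mass

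*Protocol article*

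**What the plan says.** Section 1.1 gives the published equation as "FFM (kg) = 0.883 × Body mass/WG [kg/m] + 43.674 × WG/Stature [cm/cm] − 41.480". It reports that, in a validation sample of 48 athletes, the equation correlated highly (R² = 0.900, SEE = 2.3 kg, 3.8%) "with the fat-free-mass data obtained by DXA". No adipose-tissue correction is mentioned there.

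Section 2.6 makes a general commitment to adjust this study's DXA measurements. Adipose tissue is taken as "DXA-fat mass ÷ 0.85; FFAT will be then calculated as adipose tissue × 0.15", and "DXA-derived fat-free mass will be adjusted with the subtraction of FFAT". Two reasons are given. The first is to remove the influence of FFAT on DXA fat-free mass. The second is put this way: "This has been shown to provide more accurate values to detect changes in body composition".

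Section 2.8 plans the external validation of the published equation with correlation, ICC, the concordance coefficient and "root mean squared error (RMSE) as compared to DXA measurements", plus Bland–Altman plots in which the mean difference is read as systematic error. It neither exempts this comparison from the section 2.6 adjustment nor asks for an unadjusted version alongside.

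On who is included, section 2.5.3 assigns the equation to athletes, while section 2.8 validates it in the total sample.

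**The concern.** A validation is interpretable only if prediction and reference are the same quantity. On the natural reading of section 1.1, the equation predicts DXA fat-free mass. After the section 2.6 step, the reference is DXA fat-free mass less a fixed fraction of fat mass. Part of the observed difference then comes from redefining the reference and says nothing about how the equation performs in Colombian adults.

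This part is not constant. It grows with fat mass, so it puts a fat-related trend and extra spread into the Bland–Altman plot, and it differs between strata that differ in fat mass. For an equation that is otherwise unbiased, it inflates RMSE and lowers the concordance coefficient and an agreement-type ICC. For an equation that truly runs low, it can cancel the error and make agreement look better than it is. What is at stake is the fat-free-mass half of aim (i) in section 1.2.

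**Working it through.** **Inputs**
- Adipose tissue AT = FM/0.85, FFAT = 0.15 × AT, and adjusted FFM = DXA FFM − FFAT (section 2.6). FM is DXA fat mass; FFM is fat-free mass.
- SEE of the published equation: 2.3 kg, or 3.8% (section 1.1).
- Bias = mean of D = X − Y (section 2.8), with X the prediction P and Y the reference.
- Fat mass: the article gives no values. The levels below are assumptions, shown as a range.

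The article states no size for the adjustment, so there is no figure of its own to reproduce.

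**Step 1. Size of the subtraction.** FFAT = 0.15 × FM/0.85 = 0.1765 × FM.

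**Step 2. Effect on the difference.** P − adjusted FFM = (P − DXA FFM) + 0.1765 × FM. The first term is the equation's own error. The second exists only because the reference was redefined.

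**Step 3. Size against the quoted SEE.** The last column is √(2.3² + offset²). It assumes an otherwise unbiased equation with error 2.3 kg, at a fixed fat mass.

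| Assumed fat mass (kg) | Offset (kg) | Offset / SEE | RMSE (kg) |
|---|---|---|---|
| 6 | 1.06 | 0.46 | 2.53 |
| 10 | 1.76 | 0.77 | 2.90 |
| 12 | 2.12 | 0.92 | 3.13 |
| 20 | 3.53 | 1.53 | 4.21 |
| 30 | 5.29 | 2.30 | 5.77 |

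The offset equals the SEE at 2.3/0.1765 = 13.0 kg of fat.

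**Step 4. The same on a body-fat scale.** The SEE of 2.3 kg being 3.8% implies a mean fat-free mass of 2.3/0.038 = 60.5 kg. With FM = 60.5 × p/(1 − p) for an assumed body-fat fraction p:
- 10%: FM 6.7 kg, offset 1.19 kg (0.52 SEE)
- 15%: FM 10.7 kg, offset 1.88 kg (0.82 SEE)
- 20%: FM 15.1 kg, offset 2.67 kg (1.16 SEE)
- 30%: FM 25.9 kg, offset 4.58 kg (1.99 SEE)

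**Step 5. What the adjusted quantity is.** FM/0.85 + adjusted FFM = 1.1765 FM + DXA FFM − 0.1765 FM = FM + DXA FFM. The adjusted value is therefore the complement of adipose tissue, not of fat. It is adipose-tissue-free mass under the name fat-free mass.

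**Step 6. Masking.** By step 2, an equation that truly underestimates DXA fat-free mass by 1.76 kg at 10 kg of fat would show a difference of −1.76 + 1.76 = 0 against the adjusted reference.

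**The case against.** The strongest defence is that the adjustment is deliberate, cited and placed under bias control. That is fair, and several stronger criticisms that a reader might infer do not hold.

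- *That the rationale cannot apply to a cross-sectional study.* This is true only of the supporting sentence about detecting change. The first reason, removing FFAT from the lean compartment, applies to a single scan. The adjustment is a legitimate quantity; it is the wrong comparator for this particular equation.
- *That the body compartments no longer add up.* They do add up when adjusted fat-free mass is paired with adipose tissue (step 5). They fall short only when it is paired with fat mass, and no section plans that sum.
- *That the equation will be found to overestimate, so that aim (i) returns a wrong verdict.* Observed bias is the offset plus the equation's own bias, which may have either sign. Section 2.8 sets no agreement limit, so no pass or fail is defined.
- *That new fat-free-mass equations are spoiled.* Section 1.2 promises them, but the modelling text in section 2.8 names only fat mass as the dependent variable, and fat mass is not adjusted.

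Two premises are also inferred. Section 1.1 does not say outright that the equation was built on unadjusted values, and the source study is not at hand. Section 2.8 refers to DXA without saying which version; the adjusted one follows from the general statement in section 2.6. Finally, at an assumed 6 to 12 kg of fat the offset stays below the SEE.

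These points limit the size and certainty of the problem without removing it. Nothing in the article separates the validation from the adjustment, and even 1.1 to 2.1 kg is roughly half to nine-tenths of the SEE, all in one direction.

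**Conclusion.** The point stands in a bounded form. If the published equation predicts unadjusted DXA fat-free mass, and if the section 2.6 adjustment carries into the section 2.8 comparison, the validation contains a definitional overestimation of 0.176 kg per kg of fat on top of the equation's real bias. That is about 1.1 to 2.1 kg at an assumed 6 to 12 kg of fat and 3.5 kg at 20 kg, against an SEE of 2.3 kg. The coefficient follows from the article's own constants; the kilogram figures depend on the assumed fat masses.

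The offset would be larger in the total sample (section 2.8) than in athletes alone (section 2.5.3) if the other strata carry more fat, so the difference between those two sections matters here too.

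The relative fat mass validation is not affected, provided percent fat is taken from DXA fat mass over body mass. The new fat-mass models are not affected either. The effect is confined to the fat-free-mass part of aim (i) and to any fat-free-mass model that is later added.

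**What to change.** In sections 2.6 and 2.8:
- Name unadjusted DXA fat-free mass as the reference for external validation of the published fat-free-mass equation.
- Report the comparison with the FFAT-adjusted value as a sensitivity outcome under its own name, such as adipose-tissue-free mass.
- If a new fat-free-mass equation is developed, as section 1.2 promises, state which of the two quantities it predicts.
- Say whether this validation uses athletes or the total sample, since that sets the size of any remaining difference between the two references.

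The cost is a few sentences. The adjustment starts from the unadjusted value, so that value is already available from every scan, and no measurement or participant is added.

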### 2.7. Study Size

According to Knofczynski and Mundfrom [53], to obtain (at least) a coefficient of determination (R^2^) of 0.5 with an excellent level of prediction using 3 independent variables, a total of 130 participants will be needed. Stratified probability sampling techniques will be used. Thus, the total number of participants will be divided into three strata following optimal allocation methods. A fixed cost has been assigned for each stratum (sedentary persons, C1; physically active subjects, C2; and athletes, C3, given that C3 > C2 > C1) to calculate the sample size of each population using Lagrange multipliers, given by the expression:(1)$$nh=n\;\frac{NhSh/\surd Ch}{\sum_{h=1}^{L}NhSh/\surd Ch},\;h=1,\;2,\;\ldots ,\;L$$
where, the values of *n_h_* correspond to the sample units for each stratum, *N_h_* is the maximum number of participants allowed, *C_h_* is the constant cost in all strata, *L* is the number of strata, and *S_h_* is the population quasi-variance of stratum *h*. The values obtained for the sedentary group are *n* = 54; for the physically active population group, *n* = 43; and for the athlete group, *n* = 33. To validate the new equation, the development/validation ratio will be 70/30 over the number of subjects participating in the study.

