The development of the new equations to estimate fat mass (dependent variable) from different combinations of WG with sex, physical activity level, body mass, and stature (as predictor variables) will be carried out with multiple regression models under traditional (Ordinary Least Squares method) and Bayesian approaches (limited to three independent variables). For the latter, the ‘bayesbr’ and ‘bayes.lm’ R packages will be used. Variance inflation factors will be used to detect multicollinearity among predictors in the multiple linear regression models, and autocorrelation in the residuals will be assessed through the Durbin–Watson test. The variation explained by the model will be determined by the aR^2^. Finally, the SEE will be calculated for all generated models to measure the regression’s precision, while the RMSE will be used to evaluate how close the estimated values from each equation are to the actual measured values as reported elsewhere [42]. All possible regression models will be ranked using the akaike information criterion (AIC), the Bayesian information criterion (BIC), the Mallows’ C_p_, and the Hocking’s Sp. After compliance with all of the assumptions of the multiple regression analysis (normality of residual errors will be confirmed with the Omnibus k-squared and Jarque-Bera tests), the model with the better performance that includes WG will be selected for further analysis. The predictability of the equation in the selected model will be tested in the validation sample by calculating the aR^2^, RMSE, CCC, and ICC with its respective 95% CI. The concordance analysis will be performed by means of Bland–Altman diagrams, reporting the concordance intervals at 95%. Statistical tests will be carried out using the SPSS v26 statistical package (IBM Corp., Armonk, NY, USA) and the latest version of the environment for statistical computing R [54].

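### The 130 participants in section 2.7 are the number needed to fit a three-predictor equation, but the 70/30 split of those same 130 leaves 91 to fit it and 39 to validate it

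*Protocol article*

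**What the plan says.** Section 2.7 (Study Size) takes its number from a published sample-size rule for prediction by multiple regression. The target is "to obtain (at least) a coefficient of determination (R^2^) of 0.5", and the conclusion is that "with an excellent level of prediction using 3 independent variables, a total of 130 participants will be needed".

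The same 130 are the whole study: "the total number of participants will be divided into three strata following optimal allocation methods". The allocation is given as "The values obtained for the sedentary group are *n* = 54; for the physically active population group, *n* = 43" and "for the athlete group, *n* = 33".

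The section closes with the validation of the new equation: "the development/validation ratio will be 70/30 over the number of subjects participating in the study".

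Section 2.8 (Statistical Methods) uses the full sample only for external validation of the two existing equations. The new equations are built from "different combinations of WG with sex, physical activity level, body mass, and stature (as predictor variables" by least squares and by Bayesian regression, with the note "limited to three independent variables". All possible models are ranked, one that includes waist girth is chosen, and that one is tested in the validation sample.

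**The concern.** A rule that links sample size to the quality of prediction for a given number of predictors concerns the regression that estimates the coefficients. It says nothing about the sample in which a finished equation is checked. External validation of the two published equations estimates no coefficients, so the 130 can only refer to the development of the new equation.

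The plan states this need and then removes 30% of the sample before fitting. Nothing adds the validation set on top of 130, and no separate size is given for development. As written, the sizing statement does not describe the sample that will be used.

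At stake is the second objective: how stable the new equation is, and how precisely its error and limits of agreement can be reported. The first objective uses everyone and is unaffected.

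**Working it through.** **Inputs.** From section 2.7: total 130; strata 54, 43 and 33; planning R² of at least 0.5; 3 predictors; split 70/30. From section 1.1, for comparison: R² of 0.84 for relative fat mass, 0.90 for the athletes' fat-free-mass equation, and 0.71 and 0.67 for the earlier Colombian equations.

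**The plan's own figure.** The strata add up: 54 + 43 + 33 = 130. The 130 itself comes from a cited table whose numerical definition of excellent is not in the article, so it cannot be reproduced exactly. The split arithmetic does not depend on it.

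**Split.**
- Development: 0.70 × 130 = 91.
- Validation: 0.30 × 130 = 39.
- Shortfall in development: (130 − 91)/130 = 30%.
- Total needed to keep 130 for development: 130/0.70 = 185.7, so 186 (130 + 56), which is 56 more than planned.

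**Effect at the planning R².** Simulation of least squares with 3 independent normal predictors, outcome variance 1 and R² = 0.5. The measure is the correlation between predictions from the fitted equation and from the true equation. The threshold of 0.975 is an assumption.

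| n for fitting | Share of samples at 0.975 or more | 5th percentile |
|---|---|---|
| 130 | about 95% | 0.976 |
| 91 | about 88% | 0.965 |

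So 130 is plausible for a strict criterion of this kind, and 91 falls short of the same standard.

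**Effect on prediction error.** The mean squared deviation of fitted from true prediction was 0.0161 at n = 130 and 0.0235 at n = 91. Residual variance is 0.5, so the ratio of total RMSE is √(0.5235/0.5161) = 1.007, an increase of about 0.7%.

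**R² at which 91 suffices.** For a fixed number of predictors, the required n scales approximately as (1 − R²)/R², which equals 1 at R² = 0.5. Setting 130 × (1 − R²)/R² = 91 gives R² = 1/(1 + 0.70) = 0.59. The scaled requirement is:
- R² = 0.60: 130 × 0.40/0.60 = 87
- R² = 0.67: 130 × 0.33/0.67 = 64
- R² = 0.71: 130 × 0.29/0.71 = 53
- R² = 0.84: 130 × 0.16/0.84 = 25

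These figures hold for one model fixed in advance, not for a model chosen from many in the same data.

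**Precision of validation with 39.**
- RMSE, assuming normal errors and no bias: the factors are √(39/χ²) at the 97.5% and 2.5% points of chi-square on 39 degrees of freedom, √(39/58.12) = 0.82 and √(39/23.65) = 1.28. The 95% CI is about −18% to +28%.
- Each limit of agreement: 95% half-width 1.96 × √(1/n + 1.96²/(2(n − 1))) SD of the differences. This is 0.54 SD at n = 39, 0.45 SD at n = 56 and 0.29 SD at n = 130.

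**The case against.** The best defence is that 0.5 is a floor. The plan says at least 0.5, and the equations it cites report 0.67 to 0.90. If the new equation does as well, 91 people meet the standard that 130 would meet at 0.5. This stands as far as it goes. A reader might infer that the stated quality of prediction will certainly not be reached, and the documents do not support that: the shortfall is shown only at the planning value. But the protocol does not make this argument, and it chooses among all possible models in the same 91 people, which weakens it.

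Other strong readings also go too far:

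- **Error about 45% larger.** The ratio 0.0235/0.0161 = 1.46 is on the squared scale and concerns a small part of the total. A user of the equation would see about 0.7% more RMSE.
- **Six coefficients in place of three.** Five candidate variables give six coefficients if activity level is coded as two indicators. But that is the candidate pool, the coding is not stated, and the size is set for three variables. The note that limits models to three could cover the Bayesian models only, or both approaches.
- **About 10 athletes in the validation set.** This assumes a proportional split, which is not stated, and no validation by stratum is described.
- **39 is too few.** The documents set no precision target, and section 2.8 promises 95% confidence intervals, so the imprecision will be visible. What can be said is how wide the intervals will be.

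It is also fair to say that a held-out sample is a legitimate design choice. The objection to the plan is that its size statement and its split do not fit together.

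**Conclusion.** The point holds in a limited form. Section 2.7 applies a requirement for the fitting sample to the whole study and then fits on 70% of it. The gap of 91 against 130 follows from the plan's own figures and needs no outside source.

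Its consequence is moderate. The fall from about 95% to 88% rests on the assumed threshold of 0.975, independent normal predictors and a true R² of 0.5; at about 0.6 or above it vanishes for one pre-specified three-predictor model. The effect on overall prediction error is under 1%. The clearer practical cost is in validation, where 39 people give wide intervals for RMSE and for the limits of agreement. The statement should be corrected, but the error does not invalidate the study.

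**What to change.** Either of two changes to sections 2.7 and 2.8 resolves this without more participants.

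1. **Keep the split and restate the size.** Say that 91 people develop the equation and 39 validate it. Then either drop the claim of excellent prediction, or justify it for 91 with a planning R² of about 0.6 or more and reasons for that value. Give the expected precision with 39. The cost is a few sentences.
2. **Fit the final equation on all 130.** Validate it internally by bootstrap or repeated cross-validation that repeats the whole model search in each resample, and report RMSE, concordance, bias and limits of agreement from it. The cost is protocol wording and a few lines of R code. The drawback is real: there is no longer a held-out sample untouched by model selection.

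If both 130 for development and a 30% held-out set are wanted, the total is 186, which means recruiting 56 more people.
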